#### Missing data

A case will be classified as having metabolic acidosis if it falls within the described diagnostic criteria and the arterial sample shows a pH value at least 0.03 units lower and a PCO_2 _value at least 1 kPa higher than the venous sample [18,17]. If these two latter criteria are not met, or only one sample is available, it will be considered as indicating a venous sample. Venous samples will still be considered for the diagnosis of metabolic acidosis if they meet the diagnostic criteria. If no cord blood acid base data is available, the case may still be classified as having metabolic acidosis if the neonate has acid-base data obtained in the first hour of life that fulfil the diagnostic criteria, or if a lactate value greater than 10 mmol/L is documented in association with signs of maladaptation (RDS, need for buffering etc).

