#### Umbilical cord blood analysis

All enrolled cases will be subject to immediate double cord clamping and paired cord blood sampling (umbilical artery and vein), which are prerequisites for accurate diagnosis of metabolic acidosis. Sampling into two pre-heparinised syringes should be delayed by no more than 30 minutes, air bubbles will be removed, the syringes capped, and blood analysis will occur in less than 30 minutes [17].

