#### Primary outcome measure

The primary outcome measure of this study is the incidence of fetal metabolic acidosis (defined as an umbilical artery pH < 7.05, BD_ecf _> 12 mmol/L). BD_ecf _will be calculated from pH and PCO_2 _values, according to the Siggaard-Andersen acid-base algorithm [18]. Subgroup analysis, by participating centre and by availability or non-availability of ST analysis will be carried out.

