#### Sample size

The sample size calculation is based on the primary endpoint: a metabolic acidosis incidence of about 2.8% can reasonably be assumed, as this was previously reported in an observational study conducted in one of the participating centres [11]. Since this will be the first trial to evaluate the effect of computer analysis of intrapartum fetal monitoring signals and real-time alerts on perinatal outcomes, it is not possible to find an estimate of the degree of change that is expected. The closest available parallel is the evaluation of STAN^®^ monitoring versus conventional CTG during labour. A systematic review of the first three trials that studied this issue revealed an overall relative risk for metabolic acidosis of 0.64. In the absence of a better alternative, this will be the value used for initial sample size calculation. Thus assuming a reduction in metabolic acidosis from 2.8% to 1.8%, with an alpha of 0.05, a two-sided test, and a power of 0.80, about 7320 women will need to be randomised. Accounting for a 10% loss to follow-up, the study requires the inclusion of 8133 women in order to obtain the 7320 analysable cases (3660 per arm). A pilot analysis will be conducted after enrolment of the first 1500 cases to evaluate the real incidence of metabolic acidosis, the effect of real-time alerts on its rate, and the need to recalculate the trial's sample size.

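### The paired-sample check changes no primary-outcome classification, and a venous-only sample just above the arterial cut-off counts as a non-event with the neonatal fallback closed

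*Protocol article*

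**What the plan says.** All references are to the protocol article.

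- **Primary outcome measure**: metabolic acidosis is "defined as an umbilical artery pH < 7.05" together with a base deficit above 12 mmol/L. The definition is arterial.
- **Umbilical cord blood analysis**: double clamping and paired sampling are planned for every enrolled case, "which are prerequisites for accurate diagnosis of metabolic acidosis".
- **Missing data**, pair check: a case counts if it meets the criteria and "the arterial sample shows a pH value at least 0.03 units lower", with a PCO2 "value at least 1 kPa higher than the venous sample".
- **Missing data**, failed pair or single sample: "If these two latter criteria are not met, or only one sample is available, it will be considered as indicating a venous sample".
- **Missing data**, venous samples: "Venous samples will still be considered for the diagnosis of metabolic acidosis if they meet the diagnostic criteria". No separate venous cut-off is given.
- **Missing data**, fallback: neonatal acid-base results from the first hour, or a lactate above 10 mmol/L with signs of maladaptation, may establish the diagnosis. The condition is "If no cord blood acid base data is available". The section on collection of baseline, labour and outcome data states the same limit.

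**The concern.** The check is there to confirm that the value being judged is arterial. The rule for venous samples then applies the arterial cut-off to every sample that fails, so the check decides nothing.

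The rule also treats a non-qualifying venous value as though it settled the arterial question. By the protocol's own expectation the artery has the lower pH, so a venous pH slightly above 7.05 does not exclude arterial acidosis. Having that sample nevertheless closes the neonatal fallback, so an uninformative sample is handled as more conclusive than no sample.

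At stake is the sensitivity of the primary outcome, for an event expected in about 2 to 3% of births in a trial planned at 80% power.

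**Working it through.** **1. The plan's own sample size.** Inputs from the Sample size section: control rate 2.8%, relative risk 0.64, two-sided alpha 0.05, power 0.80, 10% loss. Then p1 = 0.028, p2 = 0.64 × 0.028 = 0.01792, d = 0.01008, and p̄ is the mean of the two rates.

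- Pooled-variance formula: n0 = [1.96√(2p̄(1−p̄)) + 0.842√(p1(1−p1) + p2(1−p2))]² / d² = 3465 per arm.
- With continuity correction: n = (n0/4)[1 + √(1 + 4/(n0·d))]² = 3661 per arm. The plan has 3660.
- Inflation: 7320/0.9 = 8133.

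The plan's figure reproduces and is not in dispute.

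**2. Does the check change any classification?** Cord data present:

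| Meets cut-offs | Pair check | Route | Status |
|---|---|---|---|
| Yes | Passes | Valid arterial | Event |
| Yes | Fails, or single sample | Called venous, still counted | Event |
| No | Passes | Valid arterial | Not an event |
| No | Fails, or single sample | Called venous, criteria not met | Not an event |

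Status follows the first column alone.

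**3. Which cases are missed?** Suppose the blood is truly venous, because only the vein was sampled or both syringes came from it. With a separation of at least 0.03, an arterial pH from 7.02 to just under 7.05 goes with a venous pH of at least 7.05. Example: artery 7.03, base deficit above 12, vein 7.03 + 0.03 = 7.06. The artery would be an event, but the sample in hand is not. A wider separation extends the missed range below 7.02.

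**4. The fallback, side by side.** Take two babies with arterial pH 7.03, lactate above 10 mmol/L and signs of maladaptation. With no cord sample, the baby may be classified as an event. With a single venous sample at 7.06, the baby is not an event, because cord data exist.

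**5. Size, by assumption.** Let f be the share of babies with truly venous values only, and s the share of arterial cases whose venous values also meet the cut-offs. The documents give neither. Overall sensitivity is S = 1 − f(1 − s). Assuming f of 0.10 to 0.30 and s of 0.40 to 0.60:

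- f = 0.10: S = 1 − 0.10 × 0.40 = 0.96 (s = 0.60), or 1 − 0.10 × 0.60 = 0.94 (s = 0.40)
- f = 0.30: S = 1 − 0.30 × 0.40 = 0.88 (s = 0.60), or 1 − 0.30 × 0.60 = 0.82 (s = 0.40)

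Power at 3660 per arm is Φ[(d − 1.96·se0)/se1], with se0 pooled and se1 unpooled, no continuity correction, and both rates multiplied by S:

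| S | Control | Intervention | Power |
|---|---|---|---|
| 1.00 | 2.80% | 1.79% | 0.821 |
| 0.96 | 2.69% | 1.72% | 0.805 |
| 0.94 | 2.63% | 1.68% | 0.797 |
| 0.88 | 2.46% | 1.58% | 0.770 |
| 0.82 | 2.30% | 1.47% | 0.740 |

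The baseline is 0.821 rather than 0.80 because the plan's number includes a continuity correction.

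**6. Relative risk.** If S is equal in both arms it cancels and the relative risk stays at 0.64. If f were 15% in one arm and 25% in the other with s = 0.5, the relative risk would be multiplied by (1 − 0.075)/(1 − 0.125) = 0.925/0.875 = 1.057, or by its inverse, 0.946. At the planned rates the standard error of log RR is about 0.156, and ln(1.057) = 0.056, so the shift is about a third of a standard error.

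**The case against.** The strongest case against the point has five parts.

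- **Relabelling misses nothing by itself.** A reader might infer that calling failed pairs venous causes the missed cases. It does not: a truly arterial sample labelled venous faces the same cut-off and still counts. Misses arise only where the artery was not sampled. This stands, and it means that the share of women without a valid pair overstates the group exposed.
- **Venous positives are sound on pH.** A reader might infer that a check which removes no event lets in false events. If venous pH is below 7.05, arterial pH should be lower still, so discarding those cases would lose real events. This stands.
- **The power loss rests on outside inputs.** It also takes 2.8% to be a fully ascertained arterial incidence. That figure comes from an observational study whose sampling rules are not shown. If its arterial sampling was similarly incomplete, part of the loss is already in the 2.8%. This stands.
- **The pilot analysis after 1500 cases can reset the sample size.** It can respond to a low event rate. It measures incidence under the same rule, however, so it cannot reveal misclassification or correct a difference between arms. This stands in part.
- **Nothing shows unequal sampling.** The protocol requires the same sampling in all enrolled cases. A link through mode of delivery is conceivable, but the documents do not state one. This stands.

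None of this answers steps 2 to 4, which follow from the stated rule.

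**Conclusion.** The concern holds in a limited form. As written, the arterial-venous check has no effect on event status. Truly venous samples just above the cut-off count as non-events although arterial acidosis is possible. Those babies are also shut out of a fallback that is open to babies with no sample.

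The consequence is some loss of sensitivity, with fewer events and lower power. Its size is unknown. The range of 0.805 to 0.740 against 0.821 depends on the assumed f and s, on missed cases counting as non-events equally in both arms, and on 2.8% being fully ascertained.

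Two stronger readings are not supported. First, a reader might conclude that the relative risk is biased; that needs the venous-only share to differ by arm, which the documents do not show. Second, a reader might suppose that venous negatives are dropped while venous positives are kept, so that inclusion depends on outcome; the Missing data section nowhere excludes them.

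**What to change.** In the Missing data section:

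1. Keep counting any cord sample that meets the cut-offs as an event.
2. Classify a failed-pair or single sample that does not meet them as arterial status not established, and open the existing neonatal fallback to it instead of reserving it for babies with no cord data.
3. State how babies still unresolved enter the primary analysis. Keeping them in the denominator as non-events avoids selecting on outcome.
4. Report the share of valid pairs by arm.
5. Prespecify two sensitivity analyses: (a) valid pairs only; (b) multiple imputation of the arterial value for non-qualifying samples, allowing for uncertainty about which vessel was sampled. Imputation suits a sensitivity analysis better than the primary one: treating every such sample as venous would push truly arterial values lower and create false events.

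The cord values, Apgar score, intensive care admission and mode of delivery are already collected. The section on late outcomes seeks neonatal blood results only after metabolic acidosis, a 5-minute Apgar score below 7 or intensive care admission, so the wider fallback will reach only some of these babies unless that trigger is extended too.

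The cost is a slightly more complex outcome rule and a little more analysis work.

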#### Randomisation

After enrolment, women will be randomised to one of two arms using a 1:1 computer-generated randomisation sequence attributed to each centre by the Omniview-SisPorto^®^ 3.5 program.

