#### Late outcome and serious adverse event data collection

Cases with metabolic acidosis (umbilical artery pH < 7.05 and BE_ecf _> 12 mmol/L), 5-min Apgar score < 7, or neonatal intensive care unit admission will be further investigated by the local research midwife to evaluate whether: neonatal blood analysis was performed in the first hour of life, and its results including lactate; neonatal encephalopathy of any grade occurred in the first 72 hours of life; death of the infant occurred in the first 28 days of life; other important neonatal complications occurred in the first 7 days of life; brain ultrasound or other imaging technologies were performed in the first 7 days of life, and their results. At the same time, serious adverse events (see data safety monitoring committee, below) will be sought and reported.

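### For women without cord gases the protocol writes a route to a primary event but none to a non-event, relies on neonatal tests not scheduled for all, and leaves the denominator unclear

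*Protocol article*

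**What the plan says.** All places are in the protocol article.

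- **Umbilical cord blood analysis** plans paired cord sampling for every enrolled woman.
- **Missing data** covers failed sampling: "If no cord blood acid base data is available, the case may still be classified as having metabolic acidosis". There are two ways to qualify: neonatal acid-base values from the first hour that meet the diagnostic criteria, or a lactate above 10 mmol/L together with signs of maladaptation. Two examples of such signs are given and the list is left open. Nothing is said about a baby whose first-hour result is normal, or about a well baby who was never tested.
- **Collection of baseline, labour and outcome data** says, without direction, that neonatal data serve to assess metabolic acidosis when cord samples are lacking.
- **Late outcome and serious adverse event data collection** has the local research midwife find out whether "neonatal blood analysis was performed in the first hour of life", but only after metabolic acidosis, a 5-minute Apgar score below 7, or neonatal intensive care admission.
- **Sample size** separates randomised from analysed women: "Accounting for a 10% loss to follow-up, the study requires the inclusion of 8133 women in order to obtain the 7320 analysable cases".
- **Data analysis** states intention to treat for the primary endpoint and a relative risk with 95% confidence interval.
- **Intervention arm** and **Control arm** show that staff see alerts in one arm and none in the other.

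**The concern.** A woman without cord gases has one written way into the primary endpoint, and it leads to an event. It depends on a neonatal blood test that somebody decided to take and that is looked up only after a trigger. The first trigger is defined on umbilical artery values and so cannot apply to her. That leaves the Apgar score and neonatal unit admission, both of which are themselves secondary outcomes.

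Two things are at stake. First, if rescued events enter and comparable non-events stay out, inclusion depends on the outcome and the incidence is too high. Second, staff who have seen a red alert may take more care over cord sampling or order neonatal blood more readily. The relative risk would then partly reflect who was tested. The open list of signs adds room for judgement in the same step.

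**Working it through.** **1. The plan's own figure.** Inputs from the Sample size section: "a metabolic acidosis incidence of about 2.8% can reasonably be assumed" and "overall relative risk for metabolic acidosis of 0.64", two-sided alpha 0.05, power 0.80. Then 2.8% × 0.64 = 1.792%. The two-proportion formula without continuity correction gives n₀ = 3465 per arm. With the correction, n = (n₀/4)·[1 + √(1 + 4/(n₀·0.01008))]² = 866.25 × 2.0557² ≈ 3661 per arm, or 7322 in total, against the printed 7320. Inflation: 7320/0.9 = 8133.3, against 8133. The sample size reproduces and is not in dispute. It leaves 8133 − 7320 = 813 women outside the analysable set.

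**2. Effect on incidence.** Let m be the share without cord gases, r the share of true events among them that are rescued, and p the true risk, taken as equal with and without cord gases. If rescued events enter and the rest are excluded:

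rate = [p(1 − m) + p·m·r] / [(1 − m) + p·m·r]

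The article gives neither m nor r. I use m = 0.10, borrowing the loss allowance, and p = 0.028.

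- r = 0.5: 0.02660/0.90140 = 2.95%
- r = 0.9: 0.02772/0.90252 = 3.07%

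**3. Effect on the relative risk when there is no true effect.** Assumptions: overall risk P = 2.3% in both arms (midway between 2.8% and 1.8%), and twice the risk in women without cord gases. The risk with cord gases is then P/(1 + m), and without them 2P/(1 + m).

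*Missing 10% in both arms.* The risks are 2.091% and 4.182%. Events with cord gases: 0.9 × 2.091% = 1.882% of women. Rescued events: 0.293% at r = 0.7 and 0.167% at r = 0.4.

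- Rest excluded: 2.175/90.293 = 2.408% against 2.049/90.167 = 2.273%. The ratio is 1.06, or 0.94 with the arms swapped.
- Rest counted as non-events: 2.175/2.049 = 1.06, or 0.94.
- Equal r in both arms: 1.00 either way.

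*Missing 13% in one arm and 7% in the other, r = 0.7 or 0.4.*

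| Arm | Events, % of all randomised | Rate with the rest excluded |
|---|---|---|
| m 13%, r 0.7 | 2.141 | 2.451% |
| m 13%, r 0.4 | 1.982 | 2.273% |
| m 7%, r 0.7 | 2.210 | 2.371% |
| m 7%, r 0.4 | 2.119 | 2.276% |

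- Rest excluded, widest pair: 2.451/2.276 = 1.08, or 0.93 reversed.
- Rest counted as non-events, widest pair: 1.982/2.210 = 0.897, or 1.115 reversed.
- Cord gases only: (2.3/1.13)/(2.3/1.07) = 0.95, or 1.06 reversed.

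**4. Outer limits.** With equal risk in women with and without cord gases, 10% missing in each arm and the rest excluded, detecting 50% against 100% of missing events moves a true 1.00 to 0.95 or 1.05. Detecting none against all moves it to 0.90 or 1.11. Around a true 1.8/2.8 = 0.643, the same extremes give 0.58 to 0.71. With equal detection it stays at 0.64.

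**The case against.** The strongest reply is that this is a condensed article. Handling of missing outcomes, the denominator and sensitivity analyses are usual content of an analysis plan, and the Missing data text can be read as a rule for ascertaining the outcome. That stands for imputation and for sensitivity analyses as such. It does not cover the rule that the article does state, which is one-sided and left open in its list of signs.

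Several stronger readings are tempting, and the text does not support them.

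- *Women without cord gases can never count as non-events.* No section says so. The data collection section is neutral, and intention to treat is compatible with counting the rest as event-free. What can be said is that no route to a non-event is written.
- *The rule breaches intention to treat.* It defines an outcome and changes no allocation. The tension between analysable cases and intention to treat is an ambiguity.
- *Cord sampling is selective.* It is planned for everyone, so the issue is failed sampling followed by non-universal neonatal testing.
- *Unmasked midwives classify the endpoint.* The midwife retrieves results. Who classifies, and whether the arm is hidden, is not stated.
- *The 10% is the rate of missing cord gases.* It is a loss allowance, used above only as a stand-in.

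Abnormal first pH or lactate values are also reportable as serious adverse events in both arms, which helps to capture them. That safeguard likewise picks up abnormal results only.

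The size is limited too. At 3660 per arm and 2.3% risk, the standard error of the log relative risk is √[2 × 0.977/(3660 × 0.023)] = 0.15, so a shift to 0.94 or 1.06 is under half a standard error. Nothing in the article shows that a 30-point difference in rescue would occur.

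**Conclusion.** The point holds as a defect in a stated endpoint rule. The only written classification for women without cord gases is an event, it rests on discretionary tests, and the denominator for the others is unclear.

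Excluding the others would raise a 2.8% incidence to about 2.95% to 3.07%. Bias in the relative risk needs missing cord gases or neonatal testing to differ by arm; if both are alike, it is essentially absent. Under the differences assumed here, a true 1.00 becomes 0.93 to 1.08 with the rest excluded, and 0.897 to 1.115 with the rest counted as non-events.

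This is modest beside 0.64 and would not by itself produce the planned effect. The missing shares, the rescue shares and the doubled risk are assumptions, because the article gives none of them. The rule should be corrected, but it does not undermine the trial.

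**What to change.** - State one denominator for the primary analysis, and say how a woman with neither cord gases nor a qualifying neonatal result is counted.
- Apply the neonatal route in both directions: a qualifying normal first-hour result is a non-event, an abnormal one an event.
- Replace the open-ended signs with a closed list, fixed before any outcome is seen by arm.
- Have the co-ordinating centre classify these cases with the arm hidden.
- Report missing cord gases and first-hour neonatal testing by arm.
- Add two sensitivity analyses: cord gases only, and multiple imputation over all randomised women.

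Symmetry does not remove dependence on who was tested, so the report by arm is needed. Neither sensitivity analysis is a reference standard: cord gases alone gave 0.95 or 1.06 in the unequal-missingness example, and imputation draws on the same discretionary tests if they are in the model. That is why imputation is proposed as a sensitivity analysis and not as the primary one.

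The cost is protocol wording, some extra analysis and a slightly stricter event definition. No additional sampling is needed.

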### Local Research Co-ordinators and Local Research Midwifes

A research co-ordinator in each centre will be responsible for planning of the trial and for dissemination of information to staff. A local research midwife will contribute to these tasks, and be responsible for dissemination of information to possible participants, encouraging high levels of patient recruitment, regular and timely collection and recording of data, and provision of regular feedback to the co-ordinating centre on study progress and potential protocol violations.

### Ethical Considerations

Written informed consent from all participants will be obtained before trial enrolment. This is the first time that computer analysis of intrapartum fetal monitoring with real-time alerts is being compared with conventional fetal monitoring in a randomised trial, so there is no prior evidence of benefit for the reduction in the incidence of adverse neonatal outcomes. However, there are observational data to suggest that computer analysis of fetal monitoring signals has a higher validity in prediction of adverse outcomes [16].

The confidentiality of personal data is guaranteed by the fact that person-identifiable data will not be available to anyone outside the local healthcare team. All data transmitted to the co-ordinating centre will be anonymised automatically.

### Independent Data Safety Monitoring Committee

All serious adverse events (see below) will be reported to the Data Safety Monitoring Committee, who will evaluate their frequency regularly and determine whether there is a significantly increased incidence in the intervention group and if so, whether the study should be discontinued.

This committee will consist of a neonatologist, an obstetrician, and a statistician. Serious adverse events are defined as any of the following:

• *severe metabolic acidosis (umbilical artery pH < 7.00 and BE_ecf _> 12 mmol/L) and neonatal intensive care unit admission*

• *5-min Apgar score < 7 and neonatal intensive care unit admission*

• *First available pH value after birth < 7.05 or first available lactate value after birth > 10 mmol/L*

• *Grade II or III neonatal encephalopathy*

• *Death in the first 28 days of life*

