#### Secondary outcome measures

The secondary outcomes are: overall rates of caesarean section and of caesarean section for non-reassuring fetal state; overall rates of instrumental vaginal delivery and of instrumental vaginal delivery for non-reassuring fetal state; fetal blood sampling rates; incidence of 5-minute Apgar score < 7; need for neonatal intensive care unit admission; incidence of moderate and severe neonatal encephalopathy with a hypoxic marker; perinatal death; rate of delayed interventions (interval between red alerts - offline analysis in the control arm - and delivery in metabolic acidosis cases); internal FHR monitoring rates; tracing quality and signal loss.

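### The SAE list does not name fetal death in labour, and the case-finding criteria do not cover every listed SAE, so the safety committee could receive an incomplete count

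*Protocol article*

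**What the plan says.** In the protocol article, the section Independent Data Safety Monitoring Committee lists five kinds of SAE:

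1. severe metabolic acidosis together with NICU admission;
2. "5-min Apgar score < 7 and neonatal intensive care unit admission";
3. "First available pH value after birth < 7.05 or first available lactate value after birth > 10 mmol/L";
4. "Grade II or III neonatal encephalopathy";
5. "Death in the first 28 days of life".

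Every SAE is to go to the committee. It judges whether the incidence is raised in the intervention arm and, if so, whether to stop the trial.

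The section Late outcome and serious adverse event data collection names the babies whom the research midwife investigates further: "Cases with metabolic acidosis (umbilical artery pH < 7.05 and BE_ecf _> 12 mmol/L), 5-min Apgar score < 7, or neonatal intensive care unit admission". For these babies the midwife records, among other things, whether "death of the infant occurred in the first 28 days of life". SAEs are to be sought at the same time.

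Secondary outcome measures includes "perinatal death".

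**The concern.** The trial tests a monitoring system meant to prevent harm from hypoxia in labour. Death of the fetus during labour is the gravest such harm, yet the death item starts counting at birth. The rule for finding SAEs is also narrower than the list of SAEs it serves.

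At stake is the committee's comparison between arms. If listed events can occur in babies whom the stated rule does not single out for inquiry, the counts may fall short. The shortfall need not be equal between arms: NICU admission is a decision by staff, and staff see alerts in one arm only. Separately, the secondary outcome of perinatal death cannot be assembled from a form that asks only about deaths after birth.

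**Working it through.** No figure in the plan bears on this point, and the sample size is unaffected. The check sets the SAE list against the case-finding rule. I read the base-excess threshold in the acidosis criterion and in item 1 as a base deficit above 12 mmol/L, as in Primary outcome measure. The difference in notation is a separate matter to reconcile.

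**Fetal death in labour, item by item**

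| SAE item | Met by an intrapartum death? |
|---|---|
| 1. Severe acidosis and NICU admission | No: no NICU admission |
| 2. Apgar below 7 and NICU admission | No: no NICU admission |
| 3. First pH below 7.05, or lactate above 10 | Only if pH or lactate is measured and qualifies |
| 4. Encephalopathy grade II or III | No: cannot be graded |
| 5. Death to day 28 of life | No: no days of life |

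An Apgar score of 0 is below 7, so the case does meet an inquiry criterion, provided a score is recorded. It can then become an SAE through item 3 alone, where it counts as an acidaemia event and not as a death. The outcome fields listed under Collection of baseline, labour and outcome data are birthweight, sex, Apgar scores, cord gases and NICU admission. Fetal death is not among them.

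**Coverage of the SAE list by the inquiry criteria**

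Take three pH bands (below 7.00; 7.00 to below 7.05; 7.05 or above) and six yes/no factors: base deficit above 12, Apgar below 7, NICU admission, lactate above 10, encephalopathy grade II or III, and death by day 28.

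- Combinations in all: 3 × 2⁶ = 192.
- Combinations meeting no criterion: Apgar and NICU are both negative. Of the 3 × 2 = 6 pH and base-deficit pairs, the 2 with pH below 7.05 and base deficit above 12 are removed, leaving 4. With the three remaining factors free, 4 × 2³ = 32.

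Among those 32:

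| SAE item | Combinations that are an SAE with no criterion met |
|---|---|
| 1 | 0 (needs NICU admission) |
| 2 | 0 (needs NICU admission) |
| 3 | 2 × 8 = 16 by pH, plus 2 × 4 = 8 by lactate alone: 24 |
| 4 | 4 × 4 = 16 |
| 5 | 4 × 4 = 16 |

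These count logical possibilities, not frequencies. They show that items 1 and 2 are always covered and that items 3, 4 and 5 are not.

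**Whether other data close the gap**

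- *Cord pH:* yes, in principle. Cord sampling is planned for all enrolled cases, and arterial and venous pH are recorded on the next working day. The text does not say that a low value in these data prompts an SAE inquiry.
- *Lactate:* in part. Missing data uses a neonatal lactate when no cord gas exists, but to classify the primary outcome.
- *Encephalopathy and death by day 28:* no. They are named only in the late-outcome section, for babies who meet a criterion.

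**The case against.** The strongest reply has three parts.

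First, a reader might infer that a death in labour never reaches the committee. The document does not support that. The case meets the Apgar criterion and is investigated, and paired cord sampling is planned for every enrolled case. A hypoxic death may well show "First available pH value after birth < 7.05", and that item requires neither live birth nor NICU admission. This stands. What remains is that the event depends on a measured sample and is not reported as a death.

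Second, a reader might infer that SAEs are sought only in babies who meet a criterion, and that a low cord pH outside the criteria is never looked for. The article does not say *only*. It states without condition that all SAEs are reported, and cord pH is in the routine data for enrolled women. A journal article may also leave reporting routes to the full protocol. This too stands, which is why the conclusion is that the count could be incomplete, not that it is. It does not remove the mismatch between two rules that the article itself sets out.

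Third, the consequences are rare. That is likely for deaths, but the committee acts on small counts of grave events.

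**Conclusion.** The point holds in a limited form. As written, an intrapartum fetal death after randomisation is not an SAE as a death, and three of the five SAE items can occur in a baby who meets none of the inquiry criteria. The committee's count could therefore be incomplete, although the article promises that all SAEs are reported.

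The number of events missed cannot be derived, because the document gives no rate of intrapartum death and no SAE rate. A reader might assume 0.3 to 0.5 intrapartum deaths per 1000 and obtain 8133 × 0.0003 = 2.4 to 8133 × 0.0005 = 4.1 missed deaths. That is not supported: the rate is an outside assumption, and the result also requires that none of these deaths has a qualifying pH or lactate.

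The conclusion rests on taking the SAE list as closed, as its wording indicates, and on taking the late-outcome section as the described route for finding SAEs. A fuller protocol with a wider route would answer the second limb. It would answer the first only if it also changed the SAE definition.

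**What to change.** - In the SAE list, extend the last item so that it covers intrapartum fetal death after randomisation as well as the deaths it already names.
- On the late-outcome form, record intrapartum fetal death beside infant death to day 28, so that perinatal death can be assembled.
- Add any cord pH below 7.05 in the routine outcome data to the criteria for further inquiry. This part of item 3 is then identified from data already collected.

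The cost is wording in two sections and a few more SAE forms for babies who are acidaemic but well.

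Some gaps remain. A high lactate, encephalopathy or late death in a baby who meets no criterion would still not be singled out. Making lactate or day-28 death a criterion would not help, because the late-outcome section collects them only once a criterion is met. Finding every late death would mean following all of the planned 8133 infants to day 28, which goes well beyond a change of wording and is not proposed here.
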